#### Follow-up phase.

The protocol will be finalized with the Follow-up phase, in which the long-term effects of the intervention will be assessed at six weeks (t3) and 18 weeks post-intervention (t4). The follow-up assessments comprise clinical assessments in the clinic, HrQoL scales, and cost questionnaires for the participants. Adverse events related to training will also be monitored at each follow up session, i.e. pVAS, MAS, skin issues etc.

### Outcome measures

Alongside the technology data that will be gathered with the rehabilitation technologies during the Intervention phase, and journal and report forms (primary outcomes), demographic, clinical scales, user experience, and cost data (secondary outcomes) will be collected at five time points (Fig 1).

#### Technology data.

The feasibility of the TARGeT program will be assessed based on adherence to the therapy plan, which is determined by both attendance and training dose. Attendance is defined as daily access to the technologies, measured through log-in and log-out times recorded by the technologies. The daily training dose is defined by the daily active training time, i.e., the duration spent performing the exercises, excluding planned breaks. For deeper future analyses, also, the exercises played, the aggregated number of task repetitions as well as the progression of the challenge levels per technology will be stored. Depending on the technology and the exercise, also the kinematic, dynamic, and EMG data as well as pre-established performance measures (e.g., smoothness [47]) will be saved.

#### Journal and report forms.

Stroke survivors, caregivers, therapists, and technical personnel will log the time spent on the intervention and report any interaction with the respective other parties that were not scheduled in the protocol in journal and report forms, e.g., identified by remote monitoring, as well as any safety and technical concerns encountered. From this data, the safety of the TARGeT program will be determined.

#### Clinical scales.

The clinical upper limb status of the participants will be determined at every time point (t0 to t4) with standardized clinical scales for motor impairment (FMA and Grip strength (GS) measured by a digital dynamometer), functional performance (Action Research Arm Test (ARAT) [48], Box-and-Block Test (BBT) [49]), spasticity of the shoulder adductors, elbow, wrist, and finger flexors (MAS), and pain (pVAS).

#### Usability scales.

To assess the usability of each technology, the System Usability Scale (SUS [50]) and the Raw Task Load Index (RawTLX [51]) will be used at the mid (t1, first technology set) and post-assessment (t2, second technology set).

#### Semi-structured interviews.

Before the intervention begins, participants will be interviewed to understand prior post-stroke rehabilitation experiences and expectations towards technology-aided rehabilitation. Directly after the end of the intervention, patients will take part in an interview to assess their experience and perceived benefit from this new model of care. Similarly, also therapists’ experiences and expectations will be assessed via interviews before the trial starts and after approximately one year. All interviews consist of two parts: The first part comprises explicit questions that should be rated on a Likert scale, while the second part involves qualitative, open-ended questions. The interviews will be audio-recorded.

#### HrQoL.

The perceived quality of life of the participants will be evaluated with the standardized tools EQ-5D [52] and the Stroke Specific Quality of Life Scale (SS-QoL) [53] before the intervention (t0), immediately after the intervention (t2), and during the follow-up period (t3, t4).

#### Demographics and economic data.

Besides basic demographic data such as sex and age, data on the socio-economic status as well as the housing type and location, monthly household income, and caregiver salary will be collected for the economic analysis during the baseline assessment (t0). In addition, for the cost estimation of the TARGeT program, any change in medical consumption and productivity due to this intervention will be determined with validated questionnaires of the Institute for Medical Technology Assessment Medical Consumption Questionnaire (iMCQ) [54] and Productivity Cost Questionnaire (iPCQ) [55] which will be filled in by the participants before the intervention (t0) and during the Follow-up phase (t3, t4). Furthermore, additional cost data contributing to the overall cost of the therapy such as the salary ranges of the clinical personnel, travel costs for in-clinic and home visits, costs for technical maintenance, and electricity consumption will be estimated based on the device usage time, and all therapists, technical personnel, stroke survivors, and caregivers will be asked to report the time spent on the study in journal and report forms.

### Data management and remote monitoring of technology usage

#### Data management.

Outcomes from standardized clinical assessments, usability scales, quality of life questionnaires, subject characteristics, and cost questionnaires will be collected by therapists of TTSH and electronically stored on dedicated NHG-REDcap platforms. Technology data will be automatically transferred to the secured servers at the Future Health Technologies (FHT) program, Singapore-ETH Centre, and stored there in adequate databases. Similarly, self-reported data collected with journal and report forms will be digitized and also stored on secured servers alongside the audio recordings of the interviews. No formal data monitoring committee is planned, as the study is a feasibility trial, with safety and progress overseen by the study team.

Data will be made available upon request.

#### Remote monitoring of technology usage.

To enable therapists in the clinic to remotely monitor participants’ training at home, a data transfer structure will be set up (Fig 3). Training data of the technologies will be automatically transferred from participants’ homes to the secured servers at FHT, where data will be pre-processed and made available on a website accessible to the therapists in the clinic.

**Fig 3 pone.0355160.g003:**
[figure not shown]
Data transfer structure. Data collected with the devices at participants’ homes will be sent to the FHT server and made available on a website allowing clinicians to remotely monitor the training progress.

For this, a 4G network will be set up alongside the technologies at a participant’s home that enables automatic syncing of the technology data to dedicated servers at FHT. All data is linked to participant-specific, anonymous identifiers. These identifiers will not be associated with the personal information of participants. On these servers, these data will be partly processed such that the attendance, the training dose with the individual technology, the different exercises executed, the movement repetitions, and the performance of the participant in the different exercises per technology will be provided to the website for remote monitoring. The performance measures align with the specific goals of the exercises and the technology and have been previously validated. For example, for a coordination-focused exercise on H-Man, the smoothness performance will be displayed. For data protection reasons, the website will be hosted on a secure server at FHT and will be publicly restricted. Therapists can access the website from the clinic after logging in with a two-factor authentication. This data will inform therapists about the participants’ training activities and compliance with the therapy plans. Additionally, the platform also allows to track the amount of time that therapists spent on the monitoring.

At home, all technologies will be employed with restricted access to only the application-specific software required for the operation of the technologies. With this restriction, the usability for participants and caregivers will be enhanced and the collected data will be protected.

### Data analysis

To evaluate the feasibility and safety of the TARGeT program for post-stroke survivors, we want to test the hypothesis that participants complied with the therapy plan and confirm that no major safety-related incidents occurred and concerns are raised. Studies exploring the unsupervised training with single devices found high adherence to the therapy plan (training on at least 80% of the days [18] and for at least 30 minutes [10,18]). We expect that training with a set of technologies at home will yield similar results. For this, we will perform descriptive analyses on the adherence to the therapy plan, i.e., we will analyze the attendance data (days trained out of six weeks) and the training dose (total time trained per day relative to therapy plan). Also, we will investigate whether financial resources (monthly household income) correlate with adherence. Moreover, we will analyze the journal and report forms of the participants, caregivers, clinicians, and technical personnel (frequency and type of concern (technical, general)), and the semi-structured interview data post-intervention by clustering according to safety and feasibility concerns.

Building on previous experiences [10,18,28], we hypothesize that the selected set of technologies is highly usable also in an unsupervised setting and that the user experience of the intervention is predominantly positive from participants and therapists. To evaluate the usability, we will analyze the SUS descriptively as well as the quantitative part of the semi-structured interviews post-intervention and perform a thematic analysis of the qualitative part of the interview. For the user experience, RawTLX and the interview data will be evaluated accordingly. Additionally, therapists’ expectations and perceived benefits will be determined by a descriptive and content analysis of the respective interview parts.

To evaluate the clinical impact of the TARGeT program, a two-way repeated measures analysis of variance (ANOVA) will be conducted for each clinical scale *time point* and *intervention group* as factors. The *time point* factor (pre, mid, post, follow-up 1, follow-up 2) is intended to assess both the immediate effects of the intervention and the long-term retention of the treatment gains. We hypothesize that motor function as assessed by ARAT etc. will improve significantly during the intervention period and that these gains will be maintained at follow-up. The *intervention group* factor (TARGeT intervention, conventional therapy) will compare the effects of the TARGeT intervention on clinical scales with duration-matched conventional therapy data from previous studies and the literature [9]. In addition, the interaction between *time point* and *intervention group* will be examined to determine whether temporal changes differ between groups. We hypothesize that the clinical impact (FMA, etc.) of the TARGeT program will be comparable to that of conventional therapy, validating the program as an effective technological alternative to traditional rehabilitative methods. Any additional health benefit in terms of quality of life will be determined by descriptive analysis of the SS-QoL and EQ-5D scales. Note that if the data violates the assumptions for parametric testing (normality – Shapiro-Wilk test, homogeneity of variance – Levene’s test), we will instead utilize the non-parametric test for these comparisons (e.g., Aligned Rank Transform ANOVA).

In addition, we will analyze whether the TARGeT program has the potential to reduce costs for health systems and society (compared to conventional therapy). For this, firstly, we will estimate the average total costs for participants of the TARGeT program. Based on their socio-demographic data, an estimate for the rent (housing type and location) as well as for the commuting costs for the in-clinic session (location) will be derived. The total cost from the societal perspective estimates of the TARGeT program will include both healthcare and non-healthcare costs. Healthcare costs will be estimated using a time-driven, activity-based costing approach, by combining costs incurred from the therapist’s (for remote monitoring, etc.) and technical personnel’s time (for device setup etc.) based on time data from journal and report forms and salary ranges, rental fees and maintenance costs for devices and furniture (based on time data from journal and report forms and salary ranges), and the participant’s healthcare service consumption during the TARGeT program (based on iMCQ data). Additionally, we will estimate non-healthcare costs, such as productivity losses borne by informal caregivers assisting participants during the TARGeT program, as well as social services consumption by the participants (based on time data from journal and report forms and iPCQ data). Furthermore, we will descriptively evaluate the impact of the therapy model on healthcare service utilisation (based on iMCQ data) and on productivity loss-related costs (based on iPCQ data). Finally, we will estimate the potential cost savings associated with the TARGeT program by comparing the costs with those of conventional therapy in a clinic, which will be derived from literature [18].

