To address the increasing demand for comprehensive, high-dose therapy we aim to bring home-based technology-aided rehabilitation even further by combining the benefits of a robotic gym with home-based therapy. We propose to deploy three complementary rehabilitation technologies, each focusing on a different part of the upper limb, subsequently at stroke survivors’ homes. The technologies allow for comprehensive training, including sensory, motor, and cognitive aspects, while therapists can monitor the training progress remotely from the clinic. Specifically, these technologies are highly usable and allow for individualized therapy programs depending on the specific upper limb impairment and the changes therein over the course of rehabilitation (i.e., focus on proximal or distal parts), while drastically increasing upper limb practice intensity and duration compared to usual clinic frequencies while reducing the requirements for clinical manpower, caregiver, and travel expenses, leading to a potentially economically effective rehabilitation model.

In the following, we present the study protocol for the Technology-Assisted Rehabilitation Gym for at-home Training (TARGeT) feasibility study in which up to 30 subacute and chronic stroke survivors will undergo six weeks of unsupervised, self-administered upper limb therapy at home. Specifically, we designed this study protocol to i) investigate whether unsupervised, home-based therapy with a set of complementary rehabilitative technologies is feasible and safe for stroke survivors, ii) assess the usability and user experience of stroke survivors and therapists with respect to the proposed TARGeT program, iii) evaluate whether a clinical benefit comparable to conventional therapy as reported in [9] can be achieved, and iv) to perform an economic analysis with respect to conventional therapy with data of previous studies [18]. The outcomes of the study will inform whether the TARGeT program is a feasible, safe, and economical way to tackle the increasing demand for post-stroke upper limb neurorehabilitation.

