## Methods and analysis

### Study design, setting and participants

The study design is a clinical, single-group, open-label, pilot feasibility trial to evaluate the concept of a novel therapy concept, TARGeT program, in which three complementary neurorehabilitation technologies targeting different segments of the upper limb are deployed at stroke survivors’ homes in Singapore (Fig 1). Participants will undergo six weeks of intensive at-home therapy successively using these technologies according to tailored therapy plans while the training progress is remotely monitored by clinicians. The study will be conducted in the rehabilitation outpatient clinic of Tan Tock Seng Hospital, Clinic for Advanced Rehabilitation Therapeutics, National Healthcare Group (NHG) and in participants’ homes.

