**Fig 1 pone.0355160.g001:**
[figure not shown]
TARGeT intervention: Protocol and procedures. The protocol consists of a preparation phase in the hospital (assessments, device onboarding), a 6-week home-based intervention where participants train using the technologies, and a follow-up phase in the clinic to assess the effects of the intervention. A) Schematic participant timeline according to the SPIRIT reporting guidelines, B) illustrative protocol overview.

Ethical approvals were obtained from the NHG Domain Specific Review Boards on 13 June 2024 (ECOS reference number: 2023/00527, protocol version 2, see S2 File) and ETH Zurich Ethic Commission on 11 March 2024 (Reference number: 23 ETHICS-342). The study will be conducted according to the Declaration of Helsinki and all participants will provide signed written informed consent to the clinical team before participation. The study was registered on ClinicalTrials.gov with the following registration number: NCT06406569 on 06 May 2024. Additionally, for personal data protection and cybersecurity, approval from Singapore’s national health tech agency, Synapxe, was obtained before the commencement of the study. Results of the study will be made available in scientific publications.

This manuscript was written in accordance with the SPIRIT (Standard Protocol Items: Recommendations for Interventional Trials) guidelines [25] (see S1 File).

With reference to pilot studies, sample sizes in the range of 10–30 participants are recommended [26]. We will therefore recruit up to 30 participants, aiming for a sample size of 25, factoring in a drop-out rate of about 20% (5 participants).

The inclusion and exclusion criteria for participants were derived from experiences in previous studies with the technologies used here [9,18,27,28].

The inclusion criteria are as follows:

Clinical stroke (ischaemic or haemorrhagic) confirmed by admitting doctors and brain imaging (computed tomography (CT), CT angiography or magnetic resonance imaging)Age 21–80 yearsAt least 28 days post-strokeUpper limb motor impairment of FMA scale [29] 20–60Montreal Cognitive Assessment (MoCA) [30] > 21/30Ability to sit supported and continuously for 60 minutesStable home abode with enough space to place technologies (clear floor area of at least 1.2m x 2.0m in the proximity of a power socket)Availability of caregiver to assist in home-based exercises

Participants will not be recruited if any of the following exclusion criteria are present:

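### No major incident among 25 to 30 participants is the only stated safety benchmark, and it would still be compatible with a true incident rate of roughly 10% to 14% per participant

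*Protocol article*

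**What the plan says.** The Data analysis section gives the safety aim as to "confirm that no major safety-related incidents occurred and concerns are raised". On the natural reading, the second half means that no concerns are raised. The analysis that follows is descriptive: counts and kinds of concern from the journals and report forms, and post-intervention interviews grouped by safety and feasibility themes.

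The Outcome measures section lists the journals and report forms among the primary outcomes. Its subsection on them adds: "From this data, the safety of the TARGeT program will be determined". The Introduction says: "The outcomes of the study will inform whether the TARGeT program is a feasible, safe, and economical way" to meet rising demand for rehabilitation.

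On size, the section on study design, setting and participants says: "We will therefore recruit up to 30 participants, aiming for a sample size of 25". The basis is a pilot-study convention: "With reference to pilot studies, sample sizes in the range of 10–30 participants are recommended". There is no concurrent control: "The study design is a clinical, single-group, open-label, pilot feasibility trial".

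Other safety information is also planned. Training-related adverse events such as pain, spasticity and skin problems are checked at follow-up (Follow-up phase). Spasticity and pain are scored at all five time points (Clinical scales). Unscheduled contacts are recorded, with safety as one of their uses (Intervention phase).

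The limitations paragraph of the Discussion cautions about clinical effectiveness and comparability, about varying adherence, and about caregiver burden. It gives no caution about safety.

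**The concern.** The stated benchmark is a count of zero, and the article uses verbs of confirmation and determination for it. A zero count in 25 to 30 people describes what happened in that sample. It says little about the rate in the population unless it comes with an upper bound. The article gives no acceptable incident rate, and its sample size was not chosen for precision on safety.

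The setting makes this worth correcting. Training is unsupervised and at home, there is no concurrent group to put an incident rate in context, and safety is overseen by the study team without a formal monitoring committee (Data management). The results are meant to inform a larger trial and, according to the Abstract, wider adoption. If a zero count is carried forward as evidence of safety, later readers may assume that rates have been excluded which the trial could not exclude.

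**Working it through.** **Inputs from the article.** Target 25 participants, at most 30 recruited (Study design, setting and participants). The benchmark is zero major incidents (Data analysis).

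**Assumptions not in the article.** Confidence level 95%, shown one-sided and two-sided. Illustrative true per-participant rates of 2.5%, 5% and 10%. Participants are independent, and each is counted once, as having had at least one major incident or none.

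**Step 1: the article's own figure.** Adding 20% of 25 gives 25 × 1.20 = 30, which matches the stated maximum and the stated 5 drop-outs (5/25 = 20%). Dividing by the retained fraction gives 25/0.80 = 31.25, so 32, and 30 × 0.80 = 24. These differ from the stated figures by at most 2 participants, which does not matter here. What matters is that 25 is the number left after drop-out, while up to 30 could be exposed to the intervention. The article gives no safety bound to reproduce.

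**Step 2: exact (Clopper-Pearson) upper bound after 0 events in n.** One-sided 95%: 1 − 0.05^(1/n). Two-sided 95%: 1 − 0.025^(1/n). Rule-of-three check: 3/n.

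| n | One-sided 95% | Two-sided 95% | Rule of three |
|---|---|---|---|
| 25 | 11.3% | 13.7% | 12.0% |
| 30 | 9.5% | 11.6% | 10.0% |

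Across both choices of n and both kinds of bound, the range is 9.5% to 13.7%.

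**Step 3: probability of seeing zero events, (1 − p)^n.**

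| True rate p | n = 25 | n = 30 |
|---|---|---|
| 2.5% | 53% | 47% |
| 5% | 28% | 21% |
| 10% | 7% | 4% |

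**Step 4: participants needed for zero events to exclude a given rate.** The smallest n is ln(0.05)/ln(1 − p) one-sided, or ln(0.025)/ln(1 − p) two-sided, rounded up. Excluding 5% needs 59 participants one-sided (72 two-sided). Excluding 10% needs 29 (36). With 30 starters and no event, the trial could therefore just exclude 10% one-sided. It could not exclude 5% on either basis.

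**The case against.** The strongest reply is that the article is descriptive on safety and contains no decision rule. A reader might infer that zero incidents would lead automatically to the programme being declared safe. The documents do not support that: no sentence says so, the Introduction says only that the outcomes will inform the question, and confirming that no incident occurred can be read as a statement about this sample alone. This part of the reply stands.

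A reader might also infer that the report forms and interviews are the only safety evidence. They are not, given the pain, spasticity and skin checks and the recorded contacts. These data add useful information on milder harm, but they do not narrow the bound on major incidents.

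Nor should one infer that a zero count would be the likely result under a rate that matters. At the assumed 5%, its probability is 28% or 21%, well short of even odds. It reaches about one half only near 2.5%.

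A further reply is that an interval method is commonly left to the full protocol or analysis plan, which are not shown, and that low precision for rare harm affects every pilot of this size. Both statements are fair, so the missing interval is not itself the point. What remains is in the article's own text: the only stated benchmark is a zero count, the verbs are stronger than the sample can bear, and the limitations leave safety out.

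**Conclusion.** The concern holds in this limited form. The only stated safety benchmark is the absence of major incidents, and in 25 to 30 participants that is weak evidence. Zero events would leave true rates of up to 11.3% one-sided (13.7% two-sided) compatible with the data for 25 participants, and up to 9.5% (11.6%) for 30. The lower pair applies only if all 30 are recruited and start home training.

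The bounds rest on a 95% level and on independent participants, each classified once. The 28% and 21% chances of a zero count rest on the assumed 5% rate, which is illustrative because the article gives no relevant rate. The finding affects how the safety result is worded and reported. It does not call for a larger pilot, and it does not invalidate the trial as a feasibility study.

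**What to change.** 1. In Data analysis, replace the aim of confirming that no major incident occurred with the aim of estimating how often one occurs.
2. Report the proportion of all participants who start home training with at least one major safety-related incident, with its exact (Clopper-Pearson) 95% upper bound. State whether the bound is one-sided or two-sided. Counting everyone who starts also settles whether the denominator is the 25 aimed for or the up to 30 recruited.
3. Word the conclusion as the number of incidents observed and the rates excluded, not as *safe*. For example: none observed in 25 starters; rates above 11.3% excluded (one-sided 95%).
4. Add the low precision on safety to the limitations paragraph of the Discussion.

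This costs a few sentences and one line of output. It needs no new data, participants or procedures. It can still be done, because the article places the complete analyses after data collection ends. The one downside is a slightly less favourable safety headline.

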
Despite its innovative design, this study has several limitations. First, as a proof-of-concept feasibility study without a randomized controlled design, conclusions regarding clinical effectiveness and comparability to conventional therapy will be limited and should be interpreted with caution. Second, adherence to unsupervised home-based training may vary substantially across participants and may be influenced by unmeasured factors such as motivation, or personal circumstances. And third, caregiver experience and perceived burden are not comprehensively assessed which may prevent capturing the full impact of such a therapy program.

In summary, this protocol sets the foundation for evaluating the feasibility, usability, and safety of an unsupervised, at-home multi-technology rehabilitation model. Findings from this study are expected to inform further development and refinement of the protocol and the technologies and may ultimately contribute to establishing technology-aided home rehabilitation as a viable complement to traditional therapy paradigms.

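### The plan hypothesises comparability with conventional therapy but specifies only tests for a difference, which can contradict comparability and cannot establish it

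*Protocol article*

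**What the plan says.** Aim iii, at the end of the Introduction, is to evaluate whether the programme can achieve a clinical benefit comparable to conventional therapy. The Data analysis section assigns to this a two-way repeated-measures ANOVA for each clinical scale, with time point and intervention group as factors. The comparator is external: duration-matched conventional-therapy data from earlier studies and the literature. The time-by-group interaction "will be examined to determine whether temporal changes differ between groups". If assumptions fail, a non-parametric test such as the Aligned Rank Transform ANOVA replaces it.

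The same paragraph then gives the hypothesis, which presents the programme as a working substitute for usual rehabilitation: "We hypothesize that the clinical impact (FMA, etc.) of the TARGeT program will be comparable to that of conventional therapy, validating the program".

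On sample size, Study design, setting and participants notes that for pilot studies "sample sizes in the range of 10–30 participants are recommended", and continues "We will therefore recruit up to 30 participants", with the target given as "aiming for a sample size of 25". It gives no power, effect size or standard deviation. The Discussion, in its limitations paragraph, says that because the design is not randomised and controlled, "conclusions regarding clinical effectiveness and comparability to conventional therapy will be limited and should be interpreted with caution".

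**The concern.** The hypothesis and the test do not match. The null hypothesis of the group and interaction F tests is that there is no difference. Rejecting it speaks against comparability. Failing to reject it says only that the data were not precise enough to show a difference. The stated analysis therefore has no result that supports the stated hypothesis, and the aligned-rank fallback has the same property.

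This is not a detail left for a statistical analysis plan. The article has itself chosen the test, the hypothesis and the conclusion drawn from the hypothesis, and the three do not fit together.

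At stake is how aim iii is reported. If a non-significant interaction were taken as agreement with the hypothesis, the programme could be called comparable while its gains were truly smaller. The Discussion says the outcomes of this study will inform whether a powered randomised trial is feasible and necessary, so such a reading could carry over into that decision.

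**Working it through.** **Inputs.** From the protocol article: 25 TARGeT participants as the target sample, a difference test, and five time points. Not in the documents, so assumed: comparator size 25 (range 10 to 50), SD of FMA change 4, 6 or 8, a true deficit of 3 FMA points, and two-sided alpha 0.05.

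**1. The plan's own figure.** 25 × 1.20 = 30, which is the recruitment ceiling. Dividing instead gives 25 / 0.80 = 31.25, so 32, which is within two participants. The figure is not in dispute. It rests on a pilot rule of thumb and implies nothing about power for a group comparison.

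**2. Precision and the chance of a non-significant result.** For the between-group difference in change:

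- SE = SD × √(1/25 + 1/n₂), where n₂ is the comparator size.
- 95% CI half-width = t(0.975, 23 + n₂) × SE. The t value is 2.011 for n₂ = 25 and 2.035 for n₂ = 10.
- The chance of non-significance comes from the noncentral t distribution with noncentrality 3 / SE.

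For example, with SD 6 and n₂ = 25, SE = 6 × √0.08 = 1.697, the half-width is 2.011 × 1.697 = 3.41, and the noncentrality is 3 / 1.697 = 1.768. The chance of a non-significant result is then 59%.

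| SD of change | Non-significant, 25 v 25 | CI half-width, 25 v 25 | CI half-width, 25 v 10 |
|---|---|---|---|
| 4 | 26% | 2.27 | 3.04 |
| 6 | 59% | 3.41 | 4.57 |
| 8 | 75% | 4.55 | 6.09 |

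So even if the observed difference were exactly zero, the interval would exclude a 3-point deficit at 25 v 25 only when the SD is 4. With 10 comparators it would not exclude it at any of the three SDs.

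**3. The interaction test itself.** Take a deficit pattern of 0, 0.5, 1, 1, 1 times 3 points over the five visits, and compound symmetry.

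- The squared deviations of the pattern from its mean sum to 7.2.
- The within-person error variance is SD²/2.
- The noncentrality is (25 × 25 / 50) × 7.2 / (SD²/2) = 11.25, 5.00 and 2.81 for SD 4, 6 and 8.
- On 4 and 192 degrees of freedom, the test is non-significant in about 24%, 61% and 78% of trials.

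The omnibus test behaves much like the simple test of change.

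**4. Sensitivity to comparator size.** A true deficit of 0.5 SD (3 points at SD 6) is non-significant in 75%, 59% or 48% of trials with 10, 25 or 50 comparators. With an unlimited comparator it is still about 30%, because the 25 TARGeT participants set the floor.

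**5. What a formal claim would need.** For non-inferiority (one-sided 0.025, 80% power, true difference zero, equal groups), n per group = 2 × [(1.960 + 0.842) / margin in SD]². This gives 175, 63 and 25 per group for margins of 0.3, 0.5 and 0.8 SD. With 25 v 25, the approximate power of two one-sided equivalence tests at 0.05 is 0%, 10% and 76% at those margins.

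**The case against.** The strongest reply is that the decision rule is inferred. A reader might conclude that the plan will treat a non-significant interaction as validation. No sentence says so: the interaction is examined to see whether changes differ, and the validation clause belongs to a hypothesis, not to a success criterion. That objection stands. What remains is that the plan offers no other basis for calling the results comparable.

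The second reply is that the document already limits the inference. Clinical scales are secondary outcomes, the Discussion promises only preliminary insights and looks ahead to a possible powered trial, and the limitations paragraph urges caution on comparability. This stands as a reason for lower severity. A reader might go further and call the Data analysis section and the limitations paragraph contradictory. They are not: one states an expectation and the other restricts what may be concluded. Still, the caution is tied to the lack of a randomised controlled design, not to the unsuitability of the test, so it softens the problem without removing it.

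Third, a margin, interval reporting and the choice of a leading scale are commonly left to an analysis plan or full protocol, neither of which is shown. Their absence is not counted here. The point is the mismatch that the article itself states.

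Fourth, a reader might add a multiplicity charge, since several scales are each tested for several effects. That does not help. False-positive group differences would make comparability harder to claim, not easier, and the time effects are expected to be real.

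**Conclusion.** The point holds in a limited form. The plan states a comparability hypothesis with validation as its consequence and supplies only tests that can contradict it. Under the assumptions above, a true 3-point FMA deficit would be non-significant in about 26% to 75% of trials at 25 v 25, and the 95% interval would extend 2.27 to 4.55 points either side of the estimate (3.04 to 6.09 with 10 comparators). The width of these ranges reflects inputs the documents do not give: the SD of change, the comparator size, the size of the deficit and the alpha. The mismatch between test and hypothesis depends on none of them.

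It should be fixed, but it is not critical. It affects a secondary aim of a pilot with an external comparator, and the primary feasibility and safety conclusions do not depend on it.

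**What to change.** In the Data analysis section:

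- For each clinical scale, report the TARGeT-minus-conventional difference in change with a 95% confidence interval. Make FMA change from t0 to t2 the lead comparison.
- State that a non-significant group or interaction effect will not be taken as evidence of comparability.
- Replace the clause about validating the programme with wording such as *providing a preliminary estimate of the difference from conventional therapy*. This agrees with the Discussion's own statements on preliminary insights and caution.

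A formal claim of comparability would also need a margin fixed before the data are analysed. That is optional here. A margin does not remove confounding from a non-randomised external comparator, and with about 25 participants it would be likely to support a claim only if set near 0.8 SD.

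The cost is a few sentences and an interval computed from the same data. There is still time: the Status and timeline section has data collection running until 05 June 2026, with complete analyses after that. The downside is that the likely conclusion becomes *inconclusive* or *preliminary* rather than *comparable*.
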